## Abstract

**Background:**

A tenosynovial giant cell tumor (TGCT) is a locally aggressive benign neoplasm arising from intra- or extra-articular tissue. Diffuse TGCT (D-TGCT) most commonly develops in the knee, followed by the hip, ankle, elbow, and shoulder. Surgical removal is the only effective treatment option for the patients. However, a local recurrence rate as high as 47% has been reported. Recently, we revealed that zaltoprofen, a nonsteroidal anti-inflammatory drug possessing the ability to activate peroxisome proliferator-activated receptor gamma (PPARγ), can inhibit the proliferation of TGCT stromal cells via PPARγ. PPARγ is a ligand-activated transcription factor that belongs to the nuclear hormone receptor superfamily. It plays an important role in the differentiation of adipocytes from precursor cells and exhibits antitumorigenic effects on certain malignancies. Therefore, we are conducting this investigator-initiated clinical trial to evaluate whether zaltoprofen is safe and effective for patients with D-TGCT or unresectable localized TGCT (L-TGCT).

**Methods:**

This study is a randomized, placebo-controlled, double-blind, multicenter trial to evaluate the safety and efficacy of zaltoprofen for patients with D-TGCT or L-TGCT. For the treatment group, zaltoprofen 480 mg/day will be administered for 48 weeks; the placebo group will receive similar dosages without zaltoprofen. Twenty participants in each group are needed in this trial (40 participants total). The primary outcome is the progression-free rate at 48 weeks after treatment administration. “Progression” is defined as any serious events (1. Repetitive joint swelling due to hemorrhage, 2. Joint range of motion limitation, 3. Invasion of adjacent cartilage or bone, 4. Severe joint space narrowing, 5. Increase in tumor size) requiring surgical interventions. We hypothesize that the zaltoprofen group will have a higher progression-free rate compared to that of the placebo group at 48 weeks.

**Discussion:**

This is the first study to evaluate the efficacy of zaltoprofen in patients with D-TGCT or unresectable L-TGCT. We believe that the results of this trial will validate a novel treatment option, zaltoprofen, to stabilize disease progression for TGCT patients.

**Trial registration:**

University Hospital Medical Information Network (UMIN) Clinical Trials Registry (UMIN000025901) registered on 4/01/2017.

## Background

A tenosynovial giant cell tumor (TGCT) is a locally aggressive benign neoplasm arising from intra- or extra-articular tissue. A localized extra-articular TGCT, also known as a giant cell tumor of the tendon sheath, commonly emerges from the smaller joints including the hand and ankle/foot. It is slight more predominant in women than in men [1] and an annual incidence has been reported as approximately one in 50,000 [2]. Diffuse TGCT (D-TGCT), is a synonymous with pigmented villonodular synovitis, grows in the large joint such as the knee, hip, ankle, elbow, and shoulder. and the recurrence rete is high despite the surgical removal. An incidence of it has been reported as approximately two cases per million annually with mostly younger than 40 years and a slight female predominance [3]. Surgical removal (open or arthroscopic synovectomy) is the only effective treatment, but the local recurrence rate has been reported to be 16 to 47% [4, 5]. It has been reported that TGCT growth is driven by overexpression of colony-stimulating factor 1 (CSF1) as a result of fusion of the CSF1 gene to the collagen type VI α3 (COL6A3) promoter in the t(1;2) translocation [6]. Therefore, systemic therapies targeting the CSF1/CSF1R axis have been tested in patients with locally advanced or relapsed D-TGCT [7].

## Methods

### Overall study design

This study is a randomized, placebo-controlled, double-blind, multicenter trial, was designed by the investigators, and was accepted by the Pharmaceuticals and Medical Devices Agency (PMDA). The Center for Clinical Trials, Japan Medical Association (JMACCT) funded this trial (JMA-IIA00284). The trial network consisted of a lead site at Innovative Clinical Research Center, Kanazawa University (iCREK) (Kanazawa, Japan) and ten additional sites in Japan; Asahikawa Medical University Hospital; National Cancer Center Hospital; Fukui University Hospital; Nagoya City University Hospital; Nagoya University Hospital; Mie University Hospital; University Hospital, Kyoto Prefectural University of Medicine; Osaka City University Hospital; Okayama University Hospital; and Kyusyu University Hospital. The aim of this study is to evaluate the safety and efficacy of zaltoprofen for patients with D-TGCT or L-TGCT. For the treatment group, zaltoprofen 480 mg/day will be administered for 48 weeks. The overall follow-up schedule is shown in Table 1.1.

**Table 1 Tab1:** Assessment and evaluation schedule of this study

Assessments		Screening tests	Drug admin	Study period (weeks)												Joint puncture *^4^	CR/PR *^5^	W/D *^6^	4 weeks after final drug admin	F/U after trial
				4	8	12	16	20	24	28	32	36	40	44	48					
	Informed consent	x																		
	Randomization	x																		
	Study drug admin/ adherence check																	x		
Physical exam	Clinical findings	x	x *^3^	x	x	x	x	x	x	x	x	x	x	x	x			x	x	o
	Joint findings	x	x *^3^	x	x	x	x	x	x	x	x	x	x	x	x	x	x	o *^7^	x	o
	Joint function	x	x *^3^	x	x	x	x	x	x	x	x	x	x	x	x	x	x	o *^7^	x	o
	VAS scale	x	x *^3^	x	x	x	x	x	x	x	x	x	x	x	x	x	x	o *^7^	x	o
	Joint fluid findings															x				
	Height	x	x																	
	Weight	x	x			x			x			x			x			x	x	
	Vital signs	x	x	x	x	x	x	x	x	x	x	x	x	x	x				x	
Imaging	CT or MRI	x *^1^				x			x			x			x		x	o *^7^	o *^8^	o
	FDG-PET	x *^1^							x						x					
	X-ray	x *^1^				x			x			x			x		x	o *^7^	o *^8^	o
	12-lead ECG	x *^1^																	x	
Clinical exam	Blood test & urinalysis	x		x		x			x			x			x			x	x	
	Pregnancy test	o *^2^																		
	F/U evaluation																	x	x	o
	Adverse event																	x		
	Concomitant medications																	x		

*x* mandatory, *o* if required, *exam* examination, *VAS* visual analog scale, *CT* computed tomography, *MRI* magnetic resonance imaging, *FGD-PET*
^18^F-fluorodeoxyglucose- positron emission tomography, *ECG* electrocardiography, *F/U* follow up, *admin* administration, *CR* complete response, *PR* partial response, *W/D* withdrawal

*^1^: Can be used in 28 days before registration, *^2^: Only for women, *^3^: Must be evaluated before drug administration, *^4^: Must be evaluated before joint puncture, *^5^: Must be evaluated in 8 weeks ± 4 weeks after CR or PR, *^6^: Must be evaluated in ±7 days of final drug administration and before initiating post-treatments *^7^: Not necessary if disease progression is detected or post-treatments are initiated before “the timing of drug withdrawal” *^8^: Not necessary if disease progression is detected or post-treatments are initiated before “28 days after final drug administration” *^9^: Must be done until detection of progression or post-treatment initiation

The primary outcome of this study is the progression-free rate at 48 weeks after treatment administration. “Progression” is defined as any serious event requiring surgical intervention (Fig. 1). We hypothesize that the zaltoprofen group will have a higher progression-free rate compared to that of the placebo group at 48 weeks.

**Fig. 1 Fig1:**
[figure not shown]
Scheme of this study protocol. CT, computed tomography; ECG, electrocardiogram; MRI, magnetic resonance imaging; PET, positron emission tomography; XP, X-ray photograph; CTCAE, common terminology criteria for adverse events; CR, complete response; PR, partial response; SD, stable disease; PD, progressive disease; FDG, ^18^F-fluorodeoxyglucose; MSTS, Musculoskeletal Tumor Society

We are conducting this trial in accordance with the Declaration of Helsinki, the Ethical Guidelines for Medical and Health Research Involving Human Subjects, and all other applicable Japanese laws and guidelines. The protocol was approved by the Institutional Review Board (IRB) at Kanazawa University Hospital and each participating hospital. This study is registered at the University Hospital Medical Information Network (UMIN) Clinical Trials Registry (UMIN000025901).

### Study participants

We are recruiting D-TGCT and L-TGCT patients from April 2017 until March 2020, or until the enrollments are completed. We are including patients who meet all of the inclusion criteria (Table 2) (Fig. 1), but are excluding those who possess any of the exclusion criteria (Table 3). We are obtaining written informed consent from all the trial participants. These consent forms were also approved by the IRB. Each participant must understand the contents of the consent form before one’s acceptance. Each form must be dated and signed by both the participant and trial investigators. We also inform the participants that their medical treatment will not be affected if they refuse to participate in this trial. The consent forms are stored at each institution. The participants can drop out of the trial at any time.

**Table 2 Tab2:** Inclusion criteria

We include patients with all of the following criteria:	
1)	Patients who have been made aware of the research purpose, interests, and disadvantages of the clinical trial before starting the examination - They understand this, and written informed consent is obtained. No substitution is allowed.
2)	Patients who are diagnosed with diffuse-type tenosynovial giant cell tumor (pigmented chorionic synovitis) or unresectable localized tenosynovial giant cell tumor occurring in the knee joint or ankle by radiological and pathological findings
3)	Patient with measurable lesion based on RECIST^a^ v1.1 with at least one knee or ankle joint
4)	Patients who keep joint space in the knee or ankle joint in standing X-ray imaging
5)	Patients aged 20 years or older but less than 70 years old at the time of acquisition
6)	In the case of a pregnant woman, a patient whose pregnancy test, to be conducted during the screening period, is negative

^a^*RECIST* response evaluation criteria in solid tumors

**Table 3 Tab3:** Exclusion criteria

We exclude patients with any of the following criteria:	
1)	Patients with severe heart disease, renal disease, respiratory disease, blood disease, diabetes, coagulopathy, hepatic injury, or renal disorder
2)	Patients with gastric ulcer
3)	Patient with aspirin-induced asthma or history of aspirin
4)	Patients who have had a history of allergic symptoms such as itching and rash, or taking zaltoprofen (Soleton tablet 80 mg, Peon tablet 80 mg, etc.) previously
5)	Hypersensitivity to additives in zaltoprofen (lactose hydrate, corn starch, cellulose, silicic anhydride, hydroxypropyl cellulose, carmellose Ca, stearic acid Mg, polysorbate 80, hypromellose, titanium oxide, talc, carnauba wax) or patient with a history of hypersensitivity
6)	Patients who are administered any of the following agents within 14 days prior to enrollment: tyrosine kinase inhibitors, nonsteroidal anti-inflammatory drugs, thiazolidine derivatives, and drugs with a thiazolysine ring
7)	Patients who have an active range of motion limitation of > 20% with respect to the healthy joint
8)	Patients whose joint space has disappeared by standing position X-ray photography
9)	Patients who are inappropriate for examinations, such as MRI and PET^a^
10)	Patients who are pregnant or lactating or patients who do not agree to contraception from the final administration of the study drug to 90 days thereafter
11)	Patients who have difficulty taking oral medications
12)	Patients who were using other investigational drugs or using the investigational drug within 3 months prior to the study drug administration
13)	A patient whose investigator or clinical trial doctor judged him/her unsuitable for participation in this trial due to other reasons

^a^*MRI* magnetic resonance imaging, *PET* positron emission tomography

Please ensure that this wording is correct

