### Follow-up schedule

The overall follow-up schedule in this trial is shown in Table 1. Follow-up visits are conducted at each institution. We expect that regular follow-up visits will be scheduled every 4 weeks (± 7 days) to check the patients’ vital signs and to perform physical examinations. We will also evaluate disease progression by diagnostic imaging every 12 weeks, using X-ray, CT/MRI, or PDG-PET as scheduled. Blood tests are scheduled to be performed at 4 weeks and every 12 weeks thereafter (at the same time as diagnostic imaging). We will evaluate the primary outcome (i.e., the progression-free rate) at 48 weeks (Fig. 1). Adverse events and concomitant medications will be recorded through the trial.

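### Exclusion 10 as printed asks for contraception only after the last dose, so it leaves the 48 weeks of dosing uncovered

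*Protocol article*

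**What the plan says.** Exclusion 10 in Table 3 (Methods, Study participants) combines two conditions. The first excludes anyone pregnant or lactating. The second excludes "patients who do not agree to contraception from the final administration of the study drug to 90 days thereafter". The second condition is addressed to patients in general and is not limited to women.

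The treatment period is fixed in Methods, Overall study design: "For the treatment group, zaltoprofen 480 mg/day will be administered for 48 weeks". The Abstract gives the same duration.

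The other items on pregnancy concern entry. Inclusion 6 in Table 2 requires a negative test in the screening period. Table 1 has a row for "Pregnancy test", marked in the screening column with the footnote "Only for women".

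On who may be enrolled, inclusion 5 reads "Patients aged 20 years or older but less than 70 years old at the time of acquisition". The Background describes diffuse disease as occurring in patients "mostly younger than 40 years and a slight female predominance".

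**The concern.** A contraception criterion in a drug trial exists to prevent conception while the participant is exposed. A 90-day tail after the last dose makes sense only as an extension of cover that was already in force during treatment. As printed, the tail is the whole requirement. A site applying the criterion word for word could enrol someone who declines contraception during the 48 weeks on study drug but accepts it afterwards.

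People who could conceive are plainly within the target population, given the age limits and the Background's account of who has diffuse disease. The screening test and the exclusion of pregnant or lactating patients deal with status at entry. Neither deals with conception after dosing starts. What is at stake is participant safety and the clarity of an eligibility rule, not the statistical result.

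**Working it through.** The article gives no figure to reproduce. The check sets the texts side by side and adds one line of arithmetic.

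1. **Printed window** (Table 3, exclusion 10): from the final dose to 90 days after it.
2. **Planned dosing** (Overall study design): 48 weeks = 48 x 7 = 336 days.
3. **Overlap.** The window is anchored to the final dose, so it cannot include any day before that dose. Of the 336 planned dosing days, it reaches at most the last one. The same is true of a participant who stops early: the anchor moves forward, but every day before it is still outside the window.
4. **Comparison with the likely intention.** If cover were meant to run from first dose to 90 days after the last, it would span 336 + 90 = 426 days. The printed rule secures 90 of these, and 90 / 426 = 21%. The 336 days left out, 336 / 426 = 79%, are the days on drug. This takes the start as the first dose and full completion of treatment. Starting at consent would lengthen the uncovered part.
5. **Search for a repairing statement.** The rest of the article text was read for any mention of contraception, and there is none. The remaining pregnancy items are these:
   - Exclusion 10, first half: status at entry.
   - Inclusion 6: a test at screening.
   - Table 1, pregnancy test row: a mark at screening.

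   None of them asks for contraception during treatment.
6. **Omission or misstatement?** A condensed article may leave contraception rules to the full protocol. This one does not. It prints the rule with an explicit start and an explicit end, and the start is wrong.

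**The case against.** The best reply is that this is a fault of English in the article and not of the trial. Tables 2 and 3 contain other awkward or mistranslated terms, and an editorial query about wording was left standing beneath Table 3. That query does not say which wording it concerned, so it shows only that the text there was unsettled. Sites work from the protocol and consent forms approved by the review boards, and neither is shown. Fig. 1 was not available in the text reviewed. Exclusion 13 also lets an investigator refuse a patient judged unsuitable. All of this stands, and it limits the point to the printed criterion. It does not make the printed criterion right, and an investigator's discretion is no substitute for a stated rule.

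Four stronger readings may tempt a reader, and the documents support none of them.

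- **The investigators chose to leave dosing uncovered.** Nothing shows a deliberate choice, and a slip is the likelier explanation.
- **Participants were exposed in pregnancy.** No case is reported. The route to harm needs a patient who agrees to contraception after treatment but not during it, and a site that enrols her anyway.
- **The number affected can be estimated.** The article gives no split by sex or fertility. As worded, the criterion also applies to every participant, so a headcount of women would not describe its reach.
- **The lack of pregnancy tests during dosing is a second defect.** A condensed article may leave such tests to the full protocol. Table 1 is also damaged as extracted: the adverse-event row shows a single mark, although Follow-up schedule says adverse events are recorded throughout. Blank cells there are weak evidence.

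**Conclusion.** Exclusion 10 is wrong as written. The contraception window it prints excludes the whole of the planned 48 weeks before the last dose, and nothing else in the article text fills the gap. Confidence is high for the printed wording. Whether the trial's operative rule has the same gap cannot be settled without the approved protocol and consent form.

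The point should be acted on because it concerns participant safety and is very cheap to correct. It has no bearing on the sample size, the power or the primary comparison. It rests on two assumptions: that the clause is read in its ordinary sense, and that the unavailable Fig. 1 does not state a different window.

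**What to change.** Reword exclusion 10 so that it excludes patients who do not agree to use contraception from consent (or first dose), throughout study treatment, and until 90 days after the final dose.

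Then check the approved protocol and the consent form. If they carry the printed wording, amend both and tell the sites and current participants. If they already state the full window, publish a correction to the article.

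An optional copy-edit in the same pass: inclusion 6, "In the case of a pregnant woman, a patient whose pregnancy test, to be conducted during the screening period, is negative", evidently means a woman of childbearing potential. That edit does not change who is eligible and carries no weight in this point.

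The cost is one document check and one rewording, as an amendment or a correction. No extra patients, visits, tests or analyses are needed.

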### Randomization

We perform randomization at the time of trial registration (Fig. 1). One of the trial staff allocates participants to the two arms (1:1), one group receiving zaltoprofen and the other placebo. Randomization is performed by using a computer-generated random sequence with stratification for the size of tumor lesion and tumor location (i.e., knee or foot joints).

### Intervention and placebo

For the treatment (intervention) group, we prescribe 2 oral tablets of zaltoprofen (80 mg per tablet), 3 times daily with approximately one cup of water (~ 150 mL). For the placebo group, we prescribe 2 oral placebo tablets, 3 times daily with the same volume of water (Fig. 1). For both groups, we also prescribe a gastric mucosal protective agent in regular dosage during the study period.

### Outcomes

The primary outcome is the progression-free rate at 48 weeks after drug administration. Our definition of progression (exacerbation) is any serious event requiring surgical intervention. Exacerbation is indicated if a patient meets one of the following criteria:i).The joint circumference is increased by 2 cm or more with respect to the baseline (knee: 1 cm above patella; ankle joint: determined using the figure-eight method). If there is fluid accumulation, it is examined for the presence or absence of hematoma. An increase in joint circumference due simply to edema is not considered exacerbation.ii).The range of motion of the joint (i.e., active motion) is reduced by 20% or more with respect to the baseline (calculated by averaging three measurements with a goniometer).( i) or ii)must be detected in 2 consecutive evaluation periods conducted every 4 weeks)iii)An invasion of 5 mm or more of bone / cartilage erosion or a new lesion of bone / cartilage erosion of 5 mm or more, compared with that of baseline, is detected by computed tomography (CT) or magnetic resonance imaging (MRI).iv)An X-ray in the standing position shows the disappearance of joint space.v)An increase in the target lesion by 20% or more is determined by the response evaluation criteria in solid tumors (RECIST).( iii), iv) or v)must be detected once in any evaluation period conducted every 12 weeks).vi)Any surgical intervention for the disease that is performed for a specific reason.

We also evaluate secondary outcomes as follows:Progression-free rate (24 weeks and 48 weeks): Percentage of cases of complete response (CR), partial response (PR), and stable disease (SD, i.e., when CR and PR are unchanged for more than 4 weeks).Maximum Standardized Uptake Value (SUV) change by ^18^F-fluorodeoxyglucose- positron emission tomography (FDG-PET).Evaluation of affected limb function (baseline, 24 weeks, and 48 weeks): The Japanese Orthopedic Association score and Musculoskeletal Tumor Society (MSTS) score.Percentage of cases in which clinical benefit regarding pain, range of joint motion, and joint function compared with that of baseline is observed at 24 weeks and 48 weeks (judgment by investigators or clinical trial physicians).The types, incidence, and severity of adverse events and abnormal laboratory data (graded using common terminology criteria for adverse events (CTCAE) v4.0) will be assessed, evaluating the severity and relationship with the investigational drug (Fig. 1).

### Safety assessment

The investigator of each institutions ensure that adequate medical care is provided to a subject for any adverse events, including clinically significant laboratory values, related to the trial. All serious adverse events (SAEs) will be reported immediately to IRB of their institution and to the PI. The unblinding is permissible in case of SAEs. The PI will report to the IRB at Kanazawa University and PMDA according to the international conference on harmonisation (ICH) guideline-E6 and E2A (https://www.ich.org/home.html). The PI also will ensure the SAEs to all investigator and institution. If necessary, the independent data monitoring committee (IDMC) will be established.

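### Any SAE is enough to permit unblinding, so a patient who has not yet progressed may be unblinded while partly discretionary outcomes are still open

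*Protocol article*

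**What the plan says.** Methods, Overall study design: "This study is a randomized, placebo-controlled, double-blind, multicenter trial".

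Methods, Safety assessment: "All serious adverse events (SAEs) will be reported immediately to IRB of their institution and to the PI". Then, with no further condition: "The unblinding is permissible in case of SAEs". Onward reporting to the lead site's IRB and the regulator follows ICH E6 and E2A.

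Methods, Outcomes, on the primary event: "Our definition of progression (exacerbation) is any serious event requiring surgical intervention". It is then made operational: "Exacerbation is indicated if a patient meets one of the following criteria". Criteria i and ii are changes in joint circumference and active range of motion, each needed at two consecutive 4-weekly evaluations. Criteria iii to v are imaging thresholds, each needed once at a 12-weekly evaluation. Criterion vi is "Any surgical intervention for the disease that is performed for a specific reason".

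Among the secondary outcomes, clinical benefit at 24 and 48 weeks rests on "judgment by investigators or clinical trial physicians", and adverse events are assessed by "evaluating the severity and relationship with the investigational drug".

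Methods, Statistical analysis: the full analysis set leaves out only patients who violate the eligibility criteria or do not take the study drug. An unblinded patient therefore stays in the primary log-rank comparison.

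**The concern.** The sentence is a positive rule, not a gap left for a fuller document, and it ties access to the code to the seriousness of an event. Seriousness and the need to know the allocation are different things. Many serious events can be managed without knowing which tablets the patient took.

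The rule matters most for a patient who has an SAE unrelated to progression before week 48 and stays under assessment. If the code is opened, the people who measure the joint, judge benefit and decide on surgery may know the treatment, and so may the patient. Some of these outcomes have no objective threshold. In a trial of 40 patients a few altered decisions would be visible in the result.

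**Working it through.** **1. Inputs.** 20 patients per group, planned progression-free rates of 80% and 30%, 90% power (Sample size). Log-rank test, significance at 0.05 (Statistical analysis; two-sided is my assumption). Pilot: 10 patients, of whom 3 with ankle disease had surgery at their request at 12, 24 and 48 weeks, all with stable disease (Background).

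**2. The plan's own figure.** The article gives no figure for unblinding. The sample size, used below only as a denominator, can be reproduced with two proportions and mean rate (0.80 + 0.30)/2 = 0.55:

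n = [1.96 × √(2 × 0.55 × 0.45) + 1.2816 × √(0.80 × 0.20 + 0.30 × 0.70)]² / 0.50² = (1.379 + 0.780)² / 0.25 ≈ 18.6, so 19 per arm.

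Simulated log-rank power at 20 per arm is about 0.92. The figure of 20 is sound and this point does not affect it.

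**3. What is still open when an SAE occurs before progression.**

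| Outcome | How it is decided | Room for influence if allocation is known |
|---|---|---|
| Criterion i, circumference | Measured; bleeding to be told apart from edema; two consecutive visits | Some |
| Criterion ii, active range of motion | Goniometer, mean of three; two consecutive visits | Some, through examiner and patient effort |
| Criteria iii to v | Imaging thresholds, one detection | Less |
| Criterion vi, surgery | A decision to operate; no threshold given | Most |
| Clinical benefit, weeks 24 and 48 | Judgement of site physicians | Most |

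The pilot supports the row for criterion vi: 3/10 = 30% were operated on because they asked, not because disease had progressed. It does not show that unblinding led to any of these operations.

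**4. Size per patient.** One patient in 20 is 1/20 = 5 percentage points of that arm's 48-week rate, if nobody is lost earlier. The planned difference is 80 − 30 = 50 points, so one patient is a tenth of it.

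**5. Illustration of sensitivity (an assumption, not a forecast).** Suppose there is no true effect and 20 patients per arm, with events found at 12-weekly visits. Suppose also that k event-free placebo patients become criterion vi events at a random visit. Rejection rate of the two-sided 5% log-rank test, 6,000 simulated trials per cell:

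| k | Progression-free 30% | 50% | 80% |
|---|---|---|---|
| 0 | 5.0% | 5.4% | 5.6% |
| 1 | 7.2% | 6.3% | 5.4% |
| 2 | 11.6% | 10.1% | 9.4% |
| 3 | 18.2% | 16.3% | 16.3% |

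With no true effect the arms are interchangeable, so the same rates apply if the k patients are on zaltoprofen. The table says nothing about direction or about how likely any k is. One altered decision does little; two or three raise the false-positive rate to about 9 to 18%.

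**The case against.** **The article is a condensed text.** Who opens the code, who stays blinded and how a break is logged usually stand in the full protocol. The sentence permits unblinding and does not require it. This stands, and those procedural details are no part of the point. What remains is the condition that the article does state, which is broader than a double-blind trial needs.

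**A reader might infer that progression itself opens the code,** because the primary event is described as a serious event requiring surgery. The document does not support this. That phrase describes disease exacerbation, whereas SAE is the safety-reporting term. No SAE definition is shown, and nothing says that progression is an SAE. Criteria i to v can be met at a routine visit without one. The overlap is most plausible for surgery, but it is still an inference.

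**A reader might also multiply out the planning rates:** 20 × 0.20 = 4 and 20 × 0.70 = 14 progressions, hence 18 of 40 (45%) open to unblinding in a ratio of 14:4. These are patients whose primary event has already occurred, and later unblinding cannot change their time to event. The figures do not measure the problem.

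**Nor is a direction of bias documented.** It would need SAE rates by arm. The article gives none; it says only that zaltoprofen was well tolerated in the pilot, at 240 mg daily.

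**The window may be narrow.** It takes an SAE, a choice to open the code, and a decision then made differently. This is fair, and the article gives no means of putting a frequency on it.

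**Conclusion.** The point holds in a limited form. As worded, any SAE is sufficient ground for unblinding, with no link to the patient's care. A patient with an SAE before progression may then be assessed for surgery, joint measurements and clinical benefit by people who know the allocation.

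The size is 5 points of an arm's 48-week rate per affected patient, and the number of such patients is unknown. This rests on three assumptions: that the patient stays under assessment after the SAE, that the code is in fact opened to site staff or the patient, and that criterion vi would count surgery chosen in that knowledge. No stated figure is wrong and the sample size is unaffected. It is a cheap improvement to the wording, not a flaw that invalidates the design.

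**What to change.** In Safety assessment, replace the unblinding sentence with wording to this effect:

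*Unblinding of site staff is permitted only when the allocation is needed to manage the patient. Progression of TGCT, or surgery for it, is not in itself a ground for unblinding. The current status of criteria i to vi is recorded before the code is opened, unless urgent care prevents this.*

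The cost is one change of wording and slightly narrower access to the code. Emergency unblinding is kept, and neither the sample size nor the analysis changes.
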